#### Secondary outcomes

The SGAS is also used to examine other spatiotemporal parameters (step length, stride length, cadence, stance time symmetry ratio, double support time, and swing/stance time symmetry ratio) for two conditions (walking with and without shoes and orthoses). Furthermore, sagittal and frontal plane video (Basler Scout GigE; Basler AG, Ahrensburg, Germany), electromyography (Mobita and Porti 7 8bt; TMS﻿i, Oldenzaal, the Netherlands) and force plate recordings (OR6-7; AMTI, Watertown, MA, USA) are used to collect kinematic, electromyographic and kinetic data, respectively. One valid gait trial is collected for different conditions (walking with and without shoes, orthoses and walking aids). In addition, at the end of the intervention period, a full three-dimensional gait analysis is performed with an 8-camera VICON MX1.3 motion capture system operating at a sample rate of 100 Hertz (VICON, Oxford, United Kingdom) with two force plates in series recording at 1000 Hertz (OR6-7; AMTI, Watertown, MA, USA) positioned along a 12-metre walkway. Three valid gait trials are collected to register gait width and other kinematic and kinetic parameters that cannot be determined with the SGAS. Walking capacity is assessed with the Functional Gait Assessment (FGA), the FAC and the 10-Meter Walk Test (10MWT), all validated measurement instruments in the stroke population [33]. The FGA is a 10-item test to assess functional gait activities. The FAC is an instrument for categorising gait (in)dependency from ‘no ability to walk or with the help of two or more persons’ (FAC 0) to the ‘ability to walk independently’ (FAC 5). The 10MWT assesses comfortable and maximum walking speed. In this study, only comfortable walking speed will be recorded. Walking capacity is also assessed by a subjective walking capacity recovery score. During each visit the participant is asked to score his or her recovery of walking capacity since the onset of stroke by giving a percentage between 0 % (‘no recovery’) and 100 % (‘full recovery’). Balance control is assessed with the Berg Balance Scale [34–36] and fear of falling with the Falls Efficacy Scale I (FES-I) [37].

### Feasibility

Feasibility of the intervention is evaluated on the basis of compliance with the MFES-assisted gait training and patient satisfaction with this type of training using the MFES device. The following criteria are used: (1) MFES-assisted gait training took place during ≥75 % of all therapy sessions; and (2) patient satisfaction with MFES-assisted gait training was ≥7 on a numeric rating scale from 0 (‘most unsatisfied’) to 10 (‘most satisfied’) assessed at the end of the intervention period. Patient satisfaction with the MFES device is evaluated by a questionnaire designed for this study.

### Sample size

Due to lack of data on effect size, sample size is based on the feasibility of recruitment in one centre with an approximate yearly admission rate of 80 stroke survivors. Using an inclusion period of 3 years and estimating that 25 % of the patients are eligible and willing to participate, the sample size is set at 40 participants (20 in each group).

### Data management and statistical analysis

Data entry takes place by digital and paper case report forms. Personal information of the participants is treated confidentially. Every participant receives an identification number. This number is used on all forms so that no names or other personal information have to be used. Data is saved in a locked cabinet in a locked office and stored digitally in a trial master file for the duration of 15 years. Data quality is guaranteed by random checks of the research database and range checks for data values.

#### Descriptive statistics

Patient characteristics will be described using means, standard deviations, medians, and interquartile ranges (dependent on whether data is normally distributed or not) and percentages. Group comparisons at baseline will be performed with Student’s *t* tests, Mann–Whitney *U* tests and *χ*^2^ tests where appropriate.

#### Primary and secondary analysis

Primary efficacy analysis will be performed on an intention-to-treat basis. In addition, per protocol analyses will be performed. A linear mixed model for repeated measures will be used to analyse differences in the primary outcome and secondary outcomes. A squared time variable will be included to test for a curvilinear recovery curve. The interaction of time by intervention (MFES versus control) assesses whether the slopes of the recovery curves differ between groups. In these analyses both the intercept and the time variable are included as random effects. Group comparisons at the end of the intervention period for the three-dimensional gait analysis parameters and FES-I will be performed with Student’s *t* tests. To assess feasibility of the intervention, the proportion of participants in the intervention group who are compliant with the gait training and who scored ≥7 on the numeric rating scale will be determined. Patient satisfaction with the MFES device will be described. In all analyses, statistical uncertainty will be expressed by means of 95 % confidence intervals. Significance will be set at *p* < 0.05.

### Monitoring and quality assurance

Internal monitoring of the conduct of the study is performed once a year by researchers of the Merem Rehabilitation Centre De Trappenberg and the Academic Medical Centre Amsterdam. The completeness, accuracy, consistency, and procedures are checked according to the monitoring plan. Adverse events (AEs) of the individual participants are reported in the period from signing informed consent (introduction meeting) until the last follow-up meeting. All AEs reported spontaneously by the participant or observed by the primary researcher or staff are recorded. All AEs are followed until they have abated or a stable situation has been reached. Depending on the event, follow-up may require additional tests or medical procedures as indicated, and/or referral to the general physician or a medical specialist. Serious AEs (SAEs) are reported up to the end of study. The sponsor reports the SAEs to the MEC within 15 days after the sponsor has first knowledge of the SAE. SAEs that result in death or appear to be life threatening are reported expedited, i.e. not later than 7 days after the primary researcher has obtained first knowledge of the adverse event. The primary researcher reports the progress of the trial once a year to the MEC.

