**Methods:**

In a proof-of-principle study with a randomised controlled design, 40 adult patients with walking deficits who are admitted for inpatient rehabilitation within 31 days since the onset of stroke are randomised to either MFES-assisted gait training or conventional gait training. Gait training is delivered in 30-minute sessions each workday for up to 10 weeks. The step length symmetry ratio is the primary outcome. Blinded assessors conduct outcome assessments at baseline, every 2 weeks during the intervention period, immediately post intervention and at 3-month follow-up.

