## Background

Regaining independent gait is considered one of the primary goals in stroke rehabilitation [1–3]. In the early phase after stroke, the musculature of the affected side is often paretic or even paralytic. As a consequence, compensatory gait patterns characterised by asymmetries in spatial and temporal parameters may arise that tend to be persistent, even in patients who show substantial restoration of paretic leg motor control, perhaps due to mechanisms related to ‘learned non-use’ as has been described for the upper extremity [4]. These compensatory gait patterns are less energy-efficient and may negatively affect balance control leading to an increased risk of falls and injury as well as to limitations in functional mobility [5–8]. Furthermore, they may cause secondary complications, such as muscle shortening and joint deformation [6]. Restoration of gait symmetry can be accomplished by motor relearning and neuroplasticity, for which highly intensive, repetitive and task-specific training is essential in the early rehabilitation phase after stroke [9, 10]. The use of functional electrical stimulation (FES) timed to the gait cycle in the early phase after stroke may improve gait symmetry by enhancing neuroplasticity, preventing secondary complications, and by supporting the acquisition of an adequate compensatory strategy. Although the orthotic effects of peroneal FES (PFES) have been established, the therapeutic effect of PFES in the subacute phase has been scarcely investigated [11–19]. Furthermore, PFES assists the ankle dorsiflexion movement only during the swing phase and early stance phase of gait and does not support the more proximal movements of the lower limb. Several studies have shown that strength and range of motion of the knee flexors and extensors are associated with gait performance [20–22]. Thus, multi-channel FES (MFES) of the distal and proximal parts of the lower limb may be more effective in normalising the gait pattern by compensating for thigh and dorsiflexor muscle weakness. There is preliminary evidence of a positive therapeutic effect of MFES in early stroke rehabilitation on balance control and mobility [23–25]. However, it remains unclear whether MFES is effective for the restoration of gait symmetry. Furthermore, it remains unclear whether it is feasible to implement MFES in functional gait training including pre-gait activities. Due to the limited evidence of MFES-assisted gait training during early stroke rehabilitation we designed a proof-of-principle study. The aim of this study is to examine the feasibility and preliminary efficacy of MFES-assisted gait training on gait symmetry and walking capacity in patients in the subacute phase after stroke during their inpatient rehabilitation. We hypothesise that MFES-assisted gait training for maximally 10 weeks in the early phase after stroke is feasible and improves the step length symmetry compared to conventional gait training. I﻿﻿n this paper we describe the protocol of our study according to the SPIRIT guidelin﻿es (Additional file 1).

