
## Methods

### Design

A prospective, assessor-blinded, single-centre, proof-of-principle study with a randomised controlled two-armed parallel design is being conducted. Forty participants with gait impairments in the subacute phase after stroke who are referred for inpatient rehabilitation are randomly assigned in a 1:1 ratio to either an intervention group, receiving MFES-assisted gait training, or a control group, receiving gait training as usual. The intervention period lasts 10 weeks or until discharge from inpatient rehabilitation, whichever is sooner. Outcomes will be assessed every 2 weeks during the 10-week intervention period as well as after a 3-month follow-up period (Fig. 1).

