### Interventions

#### Control group

Participants in the control group will receive regular gait training by a physical therapist and/or movement therapist depending on their needs. Typically, per week, three to eight 30-minute sessions of gait-oriented physical therapy are given on five working days for 6 to 12 weeks. This ‘usual care’ may include individual gait training, gait training in groups, fitness training, sports, and hydrotherapy. Walking aids, orthoses, orthopaedic shoes and medication may all be used, but not lower limb FES. Participants will not be restricted in their activities. Therapists are instructed to document characteristics of the gait training (duration, frequency and content) for each participant in weekly logs.

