### Multi-channel functional electrical stimulation device

The MFES device used in this study (NESS L300^™^ Plus, Bioness, Valencia, CA, USA; CE 0473) delivers electrical pulses during gait to muscles in the affected leg to promote ankle dorsiflexion in combination with knee flexion or extension. The device consists of two cuffs (lower leg and thigh), a foot switch, and a wireless control unit that activates the system by radio frequency signals (Fig. 2). In each cuff two cotton electrodes and a stimulation unit are embedded. The electrodes of the lower leg cuff are located over the common peroneal nerve and the tibialis anterior muscle to elicit ankle dorsiflexion. The electrodes of the thigh cuff are positioned over the vastus medialis muscle to promote knee extension or over the biceps femoris brevis muscle to promote knee flexion. With this configuration, either paretic muscles can be stimulated or spastic muscles antagonised. Figure 3 illustrates some examples of positioning of the thigh cuff and timing of the upper leg stimulation expressed as percentage of the gait cycle [32]. Authorised clinicians are specially trained to fit and set the MFES device. They fit the device at baseline and evaluate the settings of the device every two-and-a-half weeks. A force-sensitive resistor in the foot switch detects the force under the foot. A dynamic gait-tracking algorithm is used to detect whether the foot is on the ground (e.g., initial contact) or in the air (e.g., heel off) by analysing the foot pressure. Average stance and swing phases are calculated by the system and data is transmitted by radio signals to the stimulation unit allowing for the synchronisation of the stimulation in accordance with the timing of gait events (gait mode). During the fitting process, the clinician sets the stimulation parameters (intensity level, phase duration, pulse rate, waveform and maximum duration of stimulation, ramp up, extension and ramp down) for the gait mode with a hand-held computer (personal digital assistant; PDA). The peroneal stimulation starts at ‘heel off’ and terminates at ‘heel contact’. Stimulation can be extended beyond heel contact to control the first rocker. The thigh stimulation – biceps femoris brevis or vastus muscles – can start and end once or twice at any segment in the gait cycle, which is determined by the clinician. Participants who cannot walk without personal assistance receive MFES treatment in the NESS L300^™^ Plus clinician mode (pre-gait and balance training) and gait mode (gait training) during individual physical therapy. The clinician mode is used to manually start and stop stimulation in the thigh and lower leg unit simultaneously. The clinician mode uses the stimulation parameters set for gait mode.

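### Adverse events are found only by spontaneous report or staff observation, so events after discharge, and falls above all, risk being under-counted in both arms

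*Protocol article*

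**What the plan says.** Monitoring and quality assurance sets both the method and the window. The method: "All AEs reported spontaneously by the participant or observed by the primary researcher or staff are recorded". The window: adverse events "are reported in the period from signing informed consent (introduction meeting) until the last follow-up meeting". No scheduled question, checklist or diary is stated beside this.

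The visit schedule is in Design: "Outcomes will be assessed every 2 weeks during the 10-week intervention period as well as after a 3-month follow-up period". The abstract's Methods agree, listing assessments at "baseline, every 2 weeks during the intervention period, immediately post intervention and at 3-month follow-up". Design also limits the contact-rich phase: "The intervention period lasts 10 weeks or until discharge from inpatient rehabilitation, whichever is sooner".

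For the control arm, Interventions says: "Therapists are instructed to document characteristics of the gait training (duration, frequency and content) for each participant in weekly logs". The intervention arm's logs add MFES intensity. Events are not among the listed items in either arm.

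Only the MFES arm has device contacts. Of the authorised clinicians the device section says: "They fit the device at baseline and evaluate the settings of the device every two-and-a-half weeks".

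On falls, the Background says that compensatory gait patterns "may negatively affect balance control leading to an increased risk of falls and injury". Secondary outcomes include a fear-of-falling scale but no count of falls.

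**The concern.** Passive capture works tolerably while people are on a ward and seen by staff on most days. It works poorly once they are home, because then it rests mainly on the participant remembering an event, thinking it relevant and mentioning it unprompted. The collection window includes that period, so the plan claims coverage that its method does not secure.

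Falls show the problem best. They are the harm that the article itself ties to asymmetric gait, and asymmetry is what the intervention is meant to reduce. With no fall count among the outcomes, any statement about falls would come from this passive route.

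The population adds to the risk. Only severe cognitive or language problems are excluded, and neglect and tactile sensation are recorded at intake. Some participants may therefore not notice or volunteer an event. This is inference: the article gives no data on it.

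At stake is the description of harms from a 40-person study that is meant to inform a larger trial. With 20 per arm, a few missed events change the picture.

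**Working it through.** The article states no adverse-event or fall rate, so there is no figure to reproduce. The check is of the schedule, followed by illustrations with stated assumptions.

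**1. Time without a stated study assessment**

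Inputs: intervention of at most 10 weeks and one assessment after a 3-month follow-up (Design). Assumptions: 3 months is 13 weeks, counted from the end of the intervention.

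- Full intervention: 13 / (10 + 13) = 13/23 = 57%.
- Discharge at an assumed 6 weeks, with two-weekly assessments ending at discharge: 13 / (6 + 13) = 13/19 = 68%.

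This is time without a stated assessment, not time without any capture. Earlier events can still be volunteered at the 3-month visit, and a participant who remains an inpatient after week 10 is still seen by staff.

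**2. What under-capture would do if equal in both arms**

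Assumed for illustration: true risk of 20% to 40% per arm, and half of affected participants detected.

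- True number affected per arm: 20 × 0.20 = 4 to 20 × 0.40 = 8.
- Number recorded per arm: 4 × 0.50 = 2 to 8 × 0.50 = 4.
- Apparent risk ratio: 0.50 / 0.50 = 1.0.

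The ratio between arms is undisturbed, but the reported frequency is halved.

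**3. How much extra contact the MFES arm has**

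Inputs: one fitting, then a settings review every 2.5 weeks. In 10 weeks the reviews fall at 2.5, 5 and 7.5, and possibly 10, so there are 3 or 4 reviews and at most 5 contacts with the fitting. Control gait therapy is typically 3 to 8 sessions a week, which is 30 to 80 in 10 weeks. The article states an equal volume of gait therapy for the intervention arm.

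- Smallest excess: 3/80 = 4%.
- Largest excess: 5/30 = 17%.

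If detection rose in proportion to contacts, the apparent risk ratio under equal true risk would be at most about 1.17. That also requires the reviews to be separate visits, which the article does not say.

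**4. Direction of any inequality**

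The satisfaction rating and device questionnaire (Feasibility) concern MFES, so they give that arm further openings to mention complaints. Against this, participants are told not to disclose allocation or therapy content to assessors (Randomisation and blinding). That gives MFES participants a reason to withhold device-related complaints at the two-weekly assessments. The influences pull in opposite directions, so the net effect cannot be signed.

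**The case against.** The strongest objection is that this is a condensed article. Event forms, prompts and falls questions are details commonly left to the full protocol, a separate monitoring plan is mentioned, and the schedule figure is not shown. This stands in part: contact between the end of training and the 3-month visit can only be called not stated, rather than absent. It does not dispose of the point, because the article does not merely omit the method. It states one, and that method is passive.

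A second objection is that the intervention period ends at discharge, so participants in both arms are inpatients throughout it, and staff observation is an explicit route. This stands, and it is why the concern is mainly about follow-up.

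A reader might go further and infer that MFES participants are watched so much more closely that MFES would look falsely harmful, perhaps by setting workday MFES sessions against the low end of the control range of three sessions a week. The documents do not support that. They state equal gait therapy, and both arms have two-weekly assessments and weekly logs. A large false risk ratio could be produced only by assuming detection shares that appear nowhere in the article.

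Nor does the article plan a between-arm test of adverse events or name safety in its aim. Falls appear as a background consequence of compensatory gait, not as a defined trial harm. Unequal capture would thus distort a description, not a planned test.

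**Conclusion.** The point holds as a risk of under-counting in both arms, concentrated in follow-up and most relevant to falls. About 57% of the collection window has no stated study assessment after a full 10-week intervention, and 68% if discharge comes at an assumed 6 weeks. How many events would be lost is unknown, since no event rate or detection share is given.

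Unequal counting between arms is possible but not shown. On contact numbers alone it would be small, and its direction is uncertain.

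The conclusion assumes that 3 months means 13 weeks from the end of the intervention, and that the full protocol adds no systematic enquiry. The primary efficacy analysis is not affected. The change is worth making because it is cheap and the data are meant to inform a larger trial.

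**What to change.** - Add the same yes/no event line to the weekly therapist logs in both arms: fall, injury, skin or pain complaint, other. Keep device-specific items here and away from the assessors.
- Ask one identical, allocation-neutral question on falls, injuries and other health events since the last contact. Put it at each existing two-weekly visit, with the existing visit reminder, and at the 3-month visit. Because it does not mention the device or therapy, assessors can stay blinded.
- Keep spontaneous and observed reports as an additional source, and record the source of each event.
- Describe solicited falls and adverse events by arm.
- If the full protocol already contains such an enquiry, state it in place of the passive wording.

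The cost is one line on an existing form and one question at existing contacts, with no added visit. More minor events will need recording and handling. Two limits remain: recall over about 3 months is imperfect, since the reminder and the visit both come late in the interval, and therapists who know the allocation may still record skin or pain complaints unequally.

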### Dissemination policy

Trial results are communicated to participants, healthcare professionals, the public, and other relevant groups via newsletters and (inter)national, peer-reviewed journals (Medline database). The results will be presented at relevant (inter)national conferences in rehabilitation and neurology. Furthermore, results will be published on websites of patient societies.

## Discussion

The aim of this study is to evaluate the therapeutic effects of up to 10 weeks of daily MFES-assisted gait training on spatiotemporal parameters, walking capacity, and motor recovery early after stroke. We hypothesise that stroke survivors will benefit from the therapeutic effect of MFES-assisted gait training by larger improvements on spatiotemporal parameters compared to conventional gait training. These data will inform the design of a sufficiently powered (multi-centre) randomised controlled trial. The strength of our study is that we investigate the effects of MFES during functional gait activities. Two out of three studies investigating MFES in the early phase after stroke applied MFES with the patient in a supine position [24, 25]. Moreover, the stimulation periods in the three studies regarding this topic were only 3–4 weeks [23–25]. There is no evidence for the minimum intensity of MFES required to enhance recovery of walking capacity in stroke survivors. Different treatment doses of electrical stimulation have been studied in the past from 15 minutes up to all day long and from once to more sessions a day. The three studies investigating MFES in the early phase after stroke applied MFES for 30–45 minutes and found positive effects on several outcomes [23–25]. In our study, MFES will be applied each workday for minimally 15 minutes to maximally 30 minutes to aim for a feasible protocol in early stroke rehabilitation. Findings from this study will provide insight into the initial effects of MFES-assisted gait training on regaining gait symmetry and several other outcomes in early stroke rehabilitation. The collection of detailed data will generate new knowledge regarding early use of MFES to promote motor and gait recovery in the early phase after stroke. If this study confirms the feasibility and initial efficacy of MFES-assisted gait training, a larger study would be warranted to further determine the effectiveness of this intervention.

